## Abstract

**Background:**

The Health Improvement and Prevention Study (HIPS) study aims to evaluate the capacity of general practice to identify patients at high risk for developing vascular disease and to reduce their risk of vascular disease and diabetes through behavioural interventions delivered in general practice and by the local primary care organization.

**Methods/Design:**

HIPS is a stratified randomized controlled trial involving 30 general practices in NSW, Australia. Practices are randomly allocated to an 'intervention' or 'control' group. General practitioners (GPs) and practice nurses (PNs) are offered training in lifestyle counselling and motivational interviewing as well as practice visits and patient educational resources. Patients enrolled in the trial present for a health check in which the GP and PN provide brief lifestyle counselling based on the 5As model (ask, assess, advise, assist, and arrange) and refer high risk patients to a diet education and physical activity program. The program consists of two individual visits with a dietician or exercise physiologist and four group sessions, after which patients are followed up by the GP or PN. In each practice 160 eligible patients aged between 40 and 64 years are invited to participate in the study, with the expectation that 40 will be eligible and willing to participate. Evaluation data collection consists of (1) a practice questionnaire, (2) GP and PN questionnaires to assess preventive care attitudes and practices, (3) patient questionnaire to assess self-reported lifestyle behaviours and readiness to change, (4) physical assessment including weight, height, body mass index (BMI), waist circumference and blood pressure, (5) a fasting blood test for glucose and lipids, (6) a clinical record audit, and (7) qualitative data collection. All measures are collected at baseline and 12 months except the patient questionnaire which is also collected at 6 months. Study outcomes before and after the intervention is compared between intervention and control groups after adjusting for baseline differences and clustering at the level of the practice.

**Discussion:**

This study will provide evidence of the effectiveness of a primary care intervention to reduce the risk of cardiovascular disease and diabetes in general practice patients. It will inform current policies and programs designed to prevent these conditions in Australian primary health care.

**Trial Registration:**

ACTRN12607000423415

## Background

The prevention and treatment of cardiovascular disease are major challenges confronting the community and the health system in Australia and internationally [1]. Given the contribution of cardiovascular disease to disease burden, the cost of inadequate prevention is high [2]. Diabetes, itself a major risk factor for ischaemic heart disease and stroke, affects 7.5% of Australians, and a further 16.3% of the population over the age of 25 years have impaired glucose metabolism [3].

There is considerable evidence for the effectiveness of interventions to prevent cardiovascular disease at the population and individual levels [4]. A simple office-based lifestyle intervention has been shown to significantly reduce total cholesterol in hypercholestrolaemic patients [5]. Intensive lifestyle interventions involving diet and exercise have also been shown to be effective in the prevention of diabetes in patients with impaired glucose tolerance and also lowering blood pressure in patients with hypertension over 6 months [5-8]. Even moderate reductions in weight has been shown to reduce the incidence of diabetes by more than one half [7-9]. Studies such as these suggest that there is a strong case for intervening in groups at high risk of developing lifestylerelated disease [10].

The Australian national health survey 2007-2008 found that the most common vascular risk factors were those related to nutrition, with over 90% of adults not meeting the recommended serves of vegetables, over half not consuming adequate amounts of fruit and 62% being overweight or obese [11]. Around one third of adults were classified as physically inactive, one in five smoked, and of the 59% of the population who drank alcohol, 21% did so at a level which would pose a risk to their health [11]. Patients who already have one or more risk factors for vascular disease may be more likely to perceive potential health risk, as well as benefits, than those who are not at risk. This may increase their motivation to participate in lifestyle change activities [12]. However, advice about risk may also increase psychological distress [13] which in turn can also impact on behaviour choices [14].

General practice is well placed to offer early interventions to modify lifestyle risk factors. It provides care across the continuum from prevention of illness to treatment and rehabilitation, and provides consultations to approximately 90% of Australians each year [15]. In 2007-08, 59% of general practice encounters were with patients who were overweight or obese, 26% with those who drank alcohol at risky levels and 17% with those who smoked daily [16]. There is evidence that lifestyle modification can be implemented in general practice and that selective interventions can bring about behaviour change in patients [17-19]. However, many studies have focused on single risk factors and have not tried to change systematically. Findings from research into interventions that have targeted multiple factors have been more equivocal [20].

Few primary care encounters in Australia involve risk-factor assessment and intervention, signifying an important gap between evidence and practice [21]. The challenge is thus to determine if interventions outside the practice can be integrated with routine clinical care in Australian general practice. Our previous research and that of others suggests that referral of high risk patients to services to support lifestyle change is infrequent [22-24].

General practice preventive care in Australia has recently been enhanced by the introduction of health checks. A "Well Person's Health Check" in general practice for people aged 45-49 was introduced in November 2006, as a once-only service for those who have one or more identifiable risk factors for chronic disease [25]. In 2008 a diabetes risk check was introduced for patients aged 40-49 which aimed to identify patients at high risk for diabetes, to introduce lifestyle interventions. Although these checks have been taken up by GPs, the referral rate of high risk patients for more intensive lifestyle interventions has been disappointingly low [26].

### Study Aim and Hypotheses

The aim of the HIPS is to evaluate the impact of a general practice intervention for patients at high risk of vascular disease on changes in behavioural and physiological risk factors (Table 1).

**Table 1 T1:** Study hypotheses

Primary Hypotheses	Secondary Hypotheses
1. In the intervention group 20% more patients who are at high risk of developing vascular disease will be offered evidence-based interventions (motivational counselling or referral to appropriate services) to modify their risk factors compared with patients in the control group.	4 Patients in the intervention group will be more likely to progress in their stage of change compared with the control group.
2 In the intervention group the self-reported attitudes and practices of general practice staff towards preventive care and behavioural risk factor management will improve compared with the control group	5 In the intervention group, a lower proportion of patients with high psychological distress (K10 score > 15) will change their behaviour compared to those who have low psychological distress (K10 score < 15)
3 The behavioural (diet, physical activity, smoking and alcohol) and physiological (weight, LDL cholesterol, blood pressure) risk factor scores of patients identified at high risk in the intervention group will be reduced over 12 months in comparison with high risk patients in the control group.	

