### Data collection

Data are collected at baseline, 6 months and 12 months from administrative staff, GPs, PNs, and patients. The questionnaires take between 10-30 minutes to complete (Table 7). These questionnaires have been piloted before their use in the trial.

**Table 7 T7:** Study instruments

Measurement	Details	Timeframe
**Practice questionnaire (PPVQ)**	• Practice capacity for preventive care including use of patient education materials, staff roles and teamwork in preventive care, and linkages between the practice and support services	**Baseline**

**GP/PN survey**	• This survey is based on questions from the *Preventive Medicine Attitudes and Activities Questionnaire (PMAAQ) *[38], and the *Vascular Interventions Survey *[39]	**Baseline & 12 Month**

**Patient's survey**	• This survey is based on the NSW Health Survey and previous research [40,41]. It includes questions about: (1) Practice attendance; (2) reported assessment and management of SNAP risk factors; (3) attendances at other services as a result of referral from the practice or self-referral; (4) self-reported fruit and vegetable intake, smoking, physical activity and alcohol intake, and attempts to change these; (5) readiness for behaviour change (stage of change) for each SNAP risk factor [42]; (6) The Kessler Psychological Distress Scale (K-10), a ten item questionnaire measuring negative emotional states in the preceding four weeks [43]; (7) The Neuroticism Scale from the Eysenck Personality Questionnaire Revised, Short form (EPQ-N-RS) [44], which represents an individual's tendency to experience psychological distress or neuroticism; (8) satisfaction with their care, using the General Practice Assessment Questionnaire (GPAQ) which includes questions in relation to satisfaction with GP and AHP visit and health check [45]	**Baseline & 6 months & 12 month**

**Patient's physical assessment**	• Includes weight, height, BMI, waist circumference and blood pressure measurement.	

**Patient's fasting blood tests**	• Patients are asked to have a fasting blood test to assess their serum lipids (total cholesterol, HDL, LDL, triglycerides) and glucose.	**Baseline & 12 month**

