#### Sample size calculation

All sample size calculations use a significance level of 5% and power of 80%, with design effects and estimated expected differences between the intervention and control groups based on previous research

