##### Reduction in behavioural risk factors

Assuming a design effect due to clustering of 1.8 and a 20% loss to follow up with estimates based on previous research [35]:

• if patients eat a standard deviation 2.1 portions of fruit and vegetables a sample of 288 in each group would have sufficient power to detect a mean 0.5 portion difference.

• if 22% smoke, a sample of 363 in each group would have sufficient power to detect a 6% difference.

• if 30% consume alcohol at risk levels, a sample of 362 in each group would have sufficient power to detect a 7% difference.

• For physical activity, a score of 2.1 in a sample of 305 in each group would have sufficient power to detect a mean 0.5 score difference.

We aim to recruit 30 general practices and identify 160 patients from each practice (total = 4800). From this we anticipate 25% responses in each group (600 patients in each group). An estimated 20% loss to follow-up will leave 480 patients in each group, of which we estimate 60% are high risk (288 patients in each group) (Figure 3).

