### Data Analysis

#### Quantitative evaluation - statistical analysis

Quantitative data analysis will be conducted using SPSS and ML-Win (Multilevel statistics for Windows). Multilevel linear models will be used for continuous response variables and multilevel logistic models for binary responses. Co-variates will be included in the analyses to adjust for baseline differences between the intervention and control groups.

The analysis will include changes in the study variables before and after the intervention in both intervention and control groups, including changes in patients' lifestyle risk factors and comparison of outcomes at 12 months between the intervention and control groups after adjusting for baseline differences.

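### Secondary hypothesis 5 compares distressed with non-distressed patients in the intervention arm only, which cannot by itself show that distress alters response; its K10 cut-offs also leave a score of 15 unassigned

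*Protocol article*

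**What the plan says.** Table 1 (Study Aim and Hypotheses) words hypothesis 5 as "In the intervention group, a lower proportion of patients with high psychological distress (K10 score > 15) will change their behaviour" and completes the comparison with "compared to those who have low psychological distress (K10 score < 15". The reference group is therefore low-distress patients in the same arm. Hypotheses 1 to 4 all name the control group as comparator; the other secondary hypothesis, for example, reads "Patients in the intervention group will be more likely to progress in their stage of change compared with the control group".

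K10 is part of the patient survey in Table 7: "The Kessler Psychological Distress Scale (K-10), a ten item questionnaire measuring negative emotional states in the preceding four weeks". The survey is scheduled at baseline, 6 and 12 months, and nothing restricts it to one arm. Under Randomisation and Blinding, practices are allocated after baseline data collection.

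The statistical analysis section plans multilevel linear and logistic models, before-and-after changes in each arm, and "comparison of outcomes at 12 months between the intervention and control groups after adjusting for baseline differences". It names no specific test for hypothesis 5. The sample size section gives no calculation for it.

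**The concern.** The stated aim is to evaluate the impact of the intervention. A comparison of high- with low-distress patients inside one arm combines two things: how distressed patients fare under any care, and whether distress changes what the intervention does for them. Only the same comparison in control practices can separate them. If hypothesis 5 were supported as worded, a reader could take it to mean that distressed patients gain less from the programme, although the gap might be equally large under usual care.

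Separately, the two K10 categories do not cover all scores, so the groups being compared are not fully defined.

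**Working it through.** The plan gives no figure for hypothesis 5, so there is nothing to reproduce. The check has three parts.

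**1. Categories.** Scores above 15 and scores below 15 together cover every value except 15, and no other section assigns it. The share scoring 15 is not given. If it were 3% to 10% (assumption), that would be 0.03 × 480 ≈ 14 to 0.10 × 480 = 48 patients per arm, or 0.03 × 288 ≈ 9 to 0.10 × 288 ≈ 29 if only high-risk patients are counted.

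**2. What the contrast estimates.** Let p be the proportion changing behaviour.

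- Within-arm contrast: W = p(high, intervention) − p(low, intervention).
- Interaction: D = W − [p(high, control) − p(low, control)].

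W equals D only if the gap in control practices is zero.

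Assumed rates: control 20% (high distress) and 35% (low); intervention 35% and 50%.

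- W = 0.35 − 0.50 = −0.15.
- Intervention effect: 0.35 − 0.20 = 0.15 in high distress and 0.50 − 0.35 = 0.15 in low distress, so D = 0.
- On the odds scale the intervention odds ratios are (0.35 × 0.80)/(0.65 × 0.20) = 2.15 in high distress and (0.50 × 0.65)/(0.50 × 0.35) = 1.86 in low distress. The interaction is null on the risk-difference scale only, but neither scale shows a weaker effect in distressed patients.

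**3. Size.** Inputs from the sample size section: 480 patients per arm after dropout, 288 of them high risk; design effect 1.8 for behavioural outcomes; 5% significance, taken as two-sided. Assumptions: the rates used here and a high-distress share of 20% to 50%.

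Worked case, 480 per arm and a 35% share. Effective numbers are 480 × 0.35/1.8 = 93.3 (high) and 480 × 0.65/1.8 = 173.3 (low).

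- Within-arm test when D = 0: SE = √(0.35 × 0.65/93.3 + 0.50 × 0.50/173.3) = 0.0623. The pooled proportion is 0.4475, giving a null SE of 0.0638. Power = Φ[(0.15 − 1.96 × 0.0638)/0.0623] = 0.655.
- Interaction test when D is truly 15 points (control 35% in both strata, intervention 35% and 50%): SE = √(0.0623² + 0.35 × 0.65/93.3 + 0.35 × 0.65/173.3) = 0.0874. Power = Φ(0.15/0.0874 − 1.96) = 0.404. This SE is 0.0874/0.0623 = 1.4 times the within-arm SE.

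Across shares of 20% to 50%:

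| Patients per arm | Design effect | Within-arm test supports hypothesis 5, D = 0 | Power of interaction test, D = 15 points |
|---|---|---|---|
| 480 | 1.8 | 0.50–0.70 | 0.30–0.43 |
| 288 | 1.8 | 0.32–0.48 | 0.20–0.28 |
| 480 | 1.0 | 0.76–0.92 | 0.49–0.67 |
| 288 | 1.0 | 0.53–0.73 | 0.32–0.46 |

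The rows with design effect 1.0 are a sensitivity check. The plan's 1.8 is meant for comparing arms, and a contrast between patients within the same practices may be inflated less.

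**The case against.** Hypothesis 5 does not literally claim effect modification. Read as a prognostic statement about intervention patients, it can be tested as worded. That stands: the limit is on what the result can be used to conclude.

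A reader might infer that the plan fixes a within-arm test as its only analysis of distress, or that it asserts that distress blunts the intervention. The documents support neither. The analysis section names no test for this hypothesis, and a fuller protocol or analysis plan may add an interaction. The policy uses listed in the Discussion include referral pathways but do not mention distress, so harm to policy is a possibility rather than something the plan sets up.

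A reader might also infer that patients scoring 15 are to be excluded. The text does not say so; one missing equals sign would explain the gap.

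Hypothesis 5 names no K10 time point, but that is detail an analysis plan may hold and is not a fault here. The Background does say "advice about risk may also increase psychological distress [13] which in turn can also impact on behaviour choices", so a baseline score would not capture distress raised by the advice itself. That is a separate question about mechanism. A baseline score answers whether existing distress alters the response, and it keeps the randomised comparison intact within each level.

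Finally, the interaction is poorly powered. That is true, and it argues for estimation rather than a confirmatory claim. It does not turn the within-arm contrast into evidence on response.

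**Conclusion.** The point holds in two limited parts. First, hypothesis 5 as worded is a non-randomised, prognostic contrast and cannot by itself show that distress alters the response to the intervention. Second, a K10 score of exactly 15 belongs to neither category.

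The first part follows from the design and needs no assumed figure. Its size does: at a design effect of 1.8, a within-arm test would support the hypothesis in about 32% to 70% of trials with no interaction on the risk-difference scale, given the assumed rates and distress shares. The number of patients scoring 15 cannot be established from the document. Only one secondary hypothesis is affected, so this is a correction worth making, not a threat to the trial's main comparisons.

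**What to change.** - Make the K10 categories exhaustive by assigning 15 to one of them, or keep K10 continuous.
- Add an arm-by-baseline-K10 interaction to the planned multilevel model using both arms. Report it with its confidence interval and on a stated scale, for example as a risk difference as well as an odds ratio.
- Keep the within-intervention-arm proportions, labelled descriptive or prognostic.

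The cost is a rewording of one secondary hypothesis and one further model term. No new data should be needed, because the survey covers both arms and baseline collection precedes allocation. The drawback is imprecision. In the worked case the 95% interval would extend about 1.96 × 0.0874 = 0.17, or 17 percentage points, either side of the estimate. The result should therefore be presented as an estimate, and a non-significant interaction should not be read as showing that distress makes no difference.

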## Methods/Design

The HIPS is a cluster-randomised controlled trial with randomisation at the practice level, conducted in general practice in the state of New South Wales (NSW), Australia.

### Recruitment

#### Recruitment of Divisions of General Practice and Practices

In Australia, general practice is supported by regional organizations known as Divisions General Practice (DGPs), part of whose role is to work with practices to improve their quality of care. This study involves three urban and two rural DGPs in NSW, which invited practices to participate in the study. Practices are identified from databases held at the DGP and are invited to participate in the study via a letter from the Division. Each DGP is asked to recruit eight practices to participate in the study (two of the urban DGPs participate as a pair, each aiming to recruit four practices). General practices are eligible to participate if they use computer-based medical records, are not involved in other research, and are located in the participating DGPs. All GPs and PNs in participating practices are invited to take part in the study (Figure 1).

**Figure 1 F1:**
[figure not shown]
**HIPS Recruitment Flowchart**.

#### Recruitment of Patients

Participating practices are asked to search their electronic records to identify a list of 160 patients who meet the selection criteria (Table 2). Previous research suggests that 25% of these will be eligible and willing to participate. The rationale for the eligibility criteria is to recruit sufficient patients with high to moderate risk of cardiovascular disease or diabetes to participate in the full intervention (both in general practice and the referral program). Patients in the 40-55 age groups are targeted by existing health checks but are less likely to have multiple risk factors or to be at high CVD or diabetes risk. Thus in this age group we are specifically targeting those who already have physiological risk factors. Patients aged 56-64 are more likely to have multiple risk factors and also to be at increased risk because of their age. The majority of general practice patients older than 64 years have already developed a chronic disease.

**Table 2 T2:** Patient selection criteria

Inclusion criteria	
• Aged 40-55 with hypertension and/or hyperlipidaemia	
• Aged 56-64	
• Attended the practice in the last 12 months	

**Exclusion criteria by practice**	**Exclusion criteria by GP**

Diagnosed or treated for:	• Has current severe illness or personal circumstances which are of overriding concern;
• Diabetes	
• Cardiovascular disease	• Is deceased (up to date medical records generally prevent this)
• Renal disease	• Is no longer a patient of the practice;
• Stroke	• Is unable to speak adequate English;
	• Has diabetes or cardiovascular disease;
	• Is unlikely to be able to read and understand the information sheet and consent form because of significant cognitive impairment (e.g. dementia.)

Up to 160 eligible patients are sent a letter from the practice, signed by their GP, advising that the practice is participating in the research and that the patient has been randomly selected to be invited to participate (if the list exceeds 160 patients, 160 are randomly selected for recruitment). An information sheet, consent form, questionnaires and a stamped envelope addressed to the project coordinator are also included. Patients are asked to read the information, sign the consent forms, complete the questionnaires, and return them if they wish to take part (Figure 1). When patients consent to participate, a letter of invitation to attend their GP for a health check and blood test form is mailed to them. The cost of the blood test and the GP visit is reimbursed by the study.

